### Stage Gate Data

Prior to assays being conducted on samples in this study, the SAFE-T Consortium will have analyzed (stage gate) data from healthy volunteers and patients with DILI in order to find a reduced set of investigational biomarkers that are associated with established DILI. This reduced set of investigational biomarkers will be those of interest for assays undertaken in this study: these will be documented in a protocol amendment when agreed.

### Biomarker Assessment and Selection

Cross-validation using all of the data from the study will be used to assess and select biomarkers and combinations of biomarkers.

### Terminology

- - 1. **Definition of Pre-treatment measurement**

Pre-treatment measurement is defined in this study as measurement prior to starting the drug treatment suspected of DILI. These data may be rarely available and likely to be restricted to ALT and total bilirubin. Such data will be used by the investigator and the adjudication committee to make a judgment on inclusion of the patient. It will be entered into the database.

### Definition of First-on-drug measurement

First-on-drug measurement is defined in this study as the first measurement during treatment and will often be the D0 baseline measurement. Sometimes the first-on- drug data will be available prior to D0 and is likely to be restricted to ALT and total bilirubin. The investigator and the adjudication committee will use such data to make a judgment on inclusion of the patient. It will be entered into the database.

### Definition of Baseline measurement (D0)

Day 0 (D0) is the first day of admission into this study when the informed consent is signed. D0 serum sample will be stored in the SAFE-T Biobank. This Baseline measurement may be performed the first day of hospitalization for DILI but could also be the First-on-drug measurement on drug.

### Normal Ranges

Normal ALT will be defined in IU/L for men and women, after centralization of 30 random samples of each participating centers to avoid variability in analytic conditions or definition of ULN (statistical definition or control group characteristics). The 30 samples per liver center will be taken at the Biobank and sent for blind analysis to the Pitié Salpêtrière Biochemistry department.

Normal total Bilirubin will be defined as <= 17 umol/l. If a proved Gilbert syndrome is present or other patent cause of unconjugated hyper bilirubinemia (e.g. hemolysis), the conjugated bilirubin will replace the total bilirubin.

No sign of significant liver fibrosis will be defined as FibroTest <=0.48 between 8 to 12 weeks. Unreliable results will be those defined by the BioPredictive algorithms

and reported in the result sheet. If FibroTest results are not reliable according to the company security algorithms, Fibroscan results can be used, with the predetermined standard cut-off <7.1 kPa for the absence of advanced fibrosis.

# Objectives

### Primary Objective

The primary objective of this study is to validate the performance of the new investigational biomarkers (or a combination of biomarkers) measured at baseline (or from baseline to W12) in its prediction of outcome. The outcome type that is considered of primary importance is whether after admittance with DILI, the patient will reach full recovery at W12.

These new biomarkers will be compared to ALT and total bilirubin, which are the "Standard of Diagnosis", by analogy with the "Standard of Care" for treatment.

### Secondary Objectives

The new biomarkers will be compared to ALT and total bilirubin, which are the "Standard of Diagnosis" (including Hy's Law), and to ActiTest which is already commercially available for the secondary objectives:

- - - Investigate the performance of investigational biomarkers from baseline D0 to Week 12) to predict:

1. A subsequent increase in total serum bilirubin of at least 10 umol/l more than the baseline value (D0) or an elevation of total bilirubin to 34 umol/l (Hy's law is TBILI 2xULN together with ALT 3xULN) at any other measurements between D1 to W12;
2. Death or severe liver complications (including transplant and complications associated with liver failure such as: hepatic encephalopathy, hemorrhage, associated liver failure complications: kidney failure, medical ventilation, circulatory dysfunction and infections.
3. Type of liver injury (hepatic, cholestatic and mixed).
4. Time to discharge from hospital.
   - - For each of the outcomes in (i) to (iii) determine the best investigational biomarker with associated thresholds.
     - For each of the outcomes in (i) to (iii) determine the best combination of biomarkers with associated threshold.
     - Type of drugs suspected in DILI will be assessed.
     - The prevalence of associated liver risk factors such as alcohol consumption, metabolic factors, history of familial liver disease, history of drug adverse events, history of recreational drugs (cocaine, ecstasy, amphetamines), combination of different drugs and herbals will be assessed and may be incorporated into statistical models.

### Patients and Methods

- 1. **Patients**

A total of 500 patients with acute DILI will be included. The duration of follow-up per patient will be 12 weeks.

### Criteria for inclusion

Consecutive patients with suspected acute DILI as defined by:

1. ALT activity exceeding 3 x ULN or ALP > 2 x ULN, within the last 4 weeks before the baseline visit
2. When pre-treatment ALT or ALP activity is available and > ULN, an increase of at least 2-fold the pre-treatment level to D0 is required
3. History of drug intake including any prescription drug, over-the-counter drug, recreational drugs (cocaine, ecstasy, amphetamines), herbal medications and food supplements during the 6-12 months prior to the DILI onset,
4. Absence of other known causes of liver injury
5. Patients with age >18 years that are capable of and willing to provide written informed consent

### Specific Groups for Inclusion

The following groups can be included in the study but will not be included in the Main Analysis Set (see Section 5.1) but analyzed separately for the performance of new biomarkers versus ALT and total bilirubin:

- Patients with Amanita Phalloides intoxication;
- Patients with acute exacerbation of a previous non-active carrier of HBV or chronic hepatitis C due to an immunosuppressive drug;
- Patients with previous history of chronic liver disease with advanced fibrosis (at least septal fibrosis) due to non alcoholic liver disease (NAFLD, NASH) or alcoholic liver disease [excessive alcohol consumption (male > 30 g/day, female > 20 g/day)];

### Criteria for exclusion

Any other likely alternative cause for the liver injury, such as acute or chronic viral hepatitis or chronic liver disease will be excluded. The list is long the most frequent being: Chronic autoimmune liver disease, Primary biliary cirrhosis (PBC), Primary sclerosing cholangitis (PSC), Extra-hepatic cholestasis, Ischemic liver damage, and presence of liver metastasis of other malignant diseases;

### Study Design

A multicenter, prospective, observational, non-interventional study in patients with suspected acute DILI.

### Methods

Proper risk assessment and signal detection as early as possible in clinical drug development are crucial to identify any potential of a drug to cause idiosyncratic liver toxicity. Given the time frame of five years for the SAFE-T consortium to achieve adequate qualification of selected liver biomarkers, it is highly unlikely that sample sizes required will be obtained when using Hy’s law only as signal definition.

For cholestatic liver injury cases, cut-off level for alkaline phosphatase will be 2 x ULN [3].

*Causality assessment:* Cases with suspected DILI should be initially ascertained by clinical judgement of the physician in charge and, subsequently, by the evaluation of an adjudication committee based on the following criteria: 1) an appropriate temporal relationship between the intake of the drug and the onset of the event, 2) the improvement of liver damage following the withdrawal of the drug if no fulminant or chronic liver failure is diagnosed, 3) exclusion of other causes of liver disease, 4) relapse following re-exposure when applicable and decided by clinicians in charge (as in chemotherapy cycles), and 5) previous reports of the adverse reaction. Cases will be further evaluated for causality assessment, by application of the Council for International Organizations of Medical Science (CIOMS)/Roussel Uclaf Causality Assessment Method (RUCAM) scale.

### Type of liver injury

A liver injury can be categorized as either hepatocellular, cholestatic or mixed type of injury as established in the international consensus meeting criteria (Benichou 1990) based on the ratio (R) of results of serum ALT to ALP relative to their upper limit of normal (ULN). Thus, the R ratio = (ALT/ ULN) / (ALP/ ULN). An R ratio > 5 denotes hepatocellular and < 2 cholestatic injury. Ratios between 2 and 5 are categorized as mixed hepatocellular-cholestatic injuries.

### DILI Biomarkers

The SAFE-T DILI team performed a careful and exhaustive review of the current literature and in house data from partners. Approximately 45 potential biomarker candidates were evaluated, using a standard set of criteria. Of the 45 initially evaluated biomarker candidates, 19 biomarkers and 21 components (2 biomarkers combine 2 components: Keratin 18/ccKeratin 18 and paraoxonase 1/Prothrombin) were recommended for clinical qualification. The core set of biomarker candidates to be assessed within the consortium comprises:

| Conjugated/Unconjugated Bile Acids |
| --- |
| Keratin 18 |
| ccKeratin 18 |
| Arginase 1 |
| LECT 2 |
| HPD |
| Regucalcin |
| ST6Gal1 |
| Alpha-1-Fetoprotein |
| GST alpha 1 |
| Osteopontin |
| Paraoxonase 1 |
| MCSF-R |
| Prothrombin |
| miR122 |
| Albumin mRNA |
| Microglobulin precursor mRNA |
| SDH |
| GLDH |
| HMGB1 |
| Hyperacetylated HMGB1 |

In addition to the DILI biomarker candidates listed above, ActiTest used for the clinical diagnosis of chronic necro-inflammatory activity will be also evaluated. ActiTest is a patented biomarker of liver necro-inflammatory histological activity initially validated in patients with chronic hepatitis C and B and with severe obesity. In patients with chronic hepatitis C, ActiTest has higher diagnosis performance than ALT for the diagnosis of the grade of necro-inflammatory histological activity using the METAVIR scoring system as reference. Specificity have been validated in healthy volunteers an in blood donors [4], and is part of the biomarkers assessed in protocol 5.

FibroTest is a patented non-invasive biomarker test that is reported to have the same diagnostic value as a biopsy. It is a multi-parametric test that utilizes a combination of 6 blood serum tests to generate a fibrosis score that is correlated with the degree of liver damage in patients with a variety of liver disease. This test is proposed, associated with ActiTest, for use as an alternative to liver biopsy for the assessment of fibrosis stage in the four more common chronic liver diseases: hepatitis C virus, hepatitis B virus, hepatitis nonalcoholic fatty liver disease (NAFLD), and alcoholic liver disease (ALD). FibroTest will not be evaluated as a biomarker of DILI-induced fibrosis as no measurement will be performed before treatment and it cannot be interpreted during an acute necrosis phase. It will be analyzed to assess the presumed fibrosis stage at 12 weeks of follow-up. The presence of chronic liver disease has been identified as an independent risk factor of DILI. If FibroTest is greater than 0.48 it is possible that the patients had a previous chronic liver disease or a sequel of the acute DILI-episode.

### Time-points of evaluation and samples management

Patients will be evaluated and will have blood sample collection: Ideally 9 samples [baseline (day 0), day 1, day 3, week 1, week 2, week 3, week 4, week 8 and week 12] and at least 3 mandatory samples (baseline, between day 5 and week 2, and between week 4 and week 12). Baseline will be defined as the day of first SAFE-T sample. The sample volume required for measuring the biomarkers is 24 ml of blood at each time-point: 10ml of blood in a dry tube, 5 ml in EDTA tube, 5ml in Li-Heparin tube and 4ml tube containing hexokinase inhibitor. The total amount of blood drawn will be 216 ml in three months in addition to routine tests (168 ml in outpatients). The potential risk of sample collection is phlebitis. This can be a local inflammation or in very rare cases, it can lead to a systemic infection. In addition 15 ml of urine will be sampled.

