### Recovery Outcome

At the end of the follow-up (at 12 weeks), the patient’s recovery outcome will be classified into 3 categories:

[1] **Full recovery**: ALT<2xULN, total bilirubin<2xULN**;**

[2] **Partial recovery** [ALT>=2xULN or total bilirubin>=2xULN, without increase in total bilirubin between D0 and W12] and patients without decrease in total bilirubin but in whom physicians considered that the decrease in ALT (**adaptive response**) allowed re-treatment of live-threatening disease such as non-liver cancer; If a patient has a re-treatment with severe complications as defined in [3] he will be classified as [3].

[3] **No recovery** including **severe complications** [biological severity (increase of total bilirubin between D0 and W12) or clinical severity (morbidity and mortality)].

Rules for dealing with data issues will be clarified in the statistical analysis plan (SAP). For example, if a patient dies from any cause (even if not directly associated with DILI) or is withdrawn/discontinues from the study, the patient’s data will be excluded from the Main Analysis Set but will be classified as per the last available measurement for the purposes of the Full Analysis Set.

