### Endpoints

### Primary Endpoint: Binary Recovery Outcome

The primary endpoint is the category 1 recovery outcome (see Section 1.6.1), that is the "full" recovery at the last visit (W12).

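### The minimum sampling schedule does not secure the week 12 ALT and total bilirubin on which the primary endpoint rests

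*Protocol*

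**What the plan says.** **Endpoint.** Section 2.1 (Primary Objective) asks whether "the patient will reach full recovery at W12". The section on the primary endpoint places it as "recovery at the last visit (W12", that is, at week 12. Section 1.6.1 (Recovery Outcome) says when the classification is made, "At the end of the follow-up (at 12 weeks), the patient’s recovery outcome will be classified into 3 categories", and defines full recovery as "ALT<2xULN, total bilirubin<2xULN".

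**Sampling.** Section 3.6.3 gives two schedules. The preferred one is "Ideally 9 samples [baseline (day 0), day 1, day 3, week 1, week 2, week 3, week 4, week 8 and week 12". The binding one is "at least 3 mandatory samples (baseline, between day 5 and week 2, and between week 4 and week 12".

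**Chemistry.** The data collection part of section 3.6.3 puts ALT and total bilirubin in the panel taken at each time-point. Nothing else in the protocol separately requires them at week 12.

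**Missing outcomes.** Section 1.6.1 leaves data-issue rules to the SAP and gives one example. Patients who die or leave the study are removed from the Main Analysis Set, and in the Full Analysis Set they are classified on their last value. Section 5.1 defines the Main Analysis Set by inclusion criteria and adjudication, not by having a week 12 value.

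**The concern.** The primary endpoint is tied to one time-point, but the binding sampling rule does not require a measurement there. A site can do everything that is mandatory and still leave a patient without the two laboratory values that decide the primary outcome.

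This is more than a detail for the SAP. The SAP can say how a missing outcome is handled, but it cannot create a measurement that the protocol did not ask sites to take.

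At stake is how completely the outcome behind the primary comparison of the new biomarkers with ALT and total bilirubin is observed. The three-category secondary outcome shares the gap, because partial and no recovery depend on the change in bilirubin from D0 to week 12. So does the fibrosis check in section 1.7.4, which needs a FibroTest result from weeks 8 to 12. A week 4 sample serves neither.

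**Working it through.** **1. The plan's own figure in this section.** The tube volumes add up to 10 + 5 + 5 + 4 = 24 ml per time-point. Nine time-points give 9 × 24 = 216 ml, which matches the stated total. The outpatient figure of 168 ml gives 168 / 24 = 7 samples. The arithmetic is sound. It shows that the plan budgets for well over three samples in outpatients, but it does not say which seven.

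**2. The minimum schedule against the endpoint.**

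| Requirement | Earliest day that satisfies it |
|---|---|
| Baseline sample | day 0 |
| Second mandatory sample | day 5 |
| Third mandatory sample | week 4 = 4 × 7 = day 28 |
| Primary endpoint | week 12 = 12 × 7 = day 84 |

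The largest gap between the last mandatory measurement and the endpoint is 84 − 28 = 56 days. The last guaranteed measurement then falls at 28 / 84 = one third of follow-up.

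**3. Whether another rule fills the gap.** The patient in question has neither died nor left the study, so the example in section 1.6.1 does not apply. Section 5.1 does not remove the patient from the Main Analysis Set. The patient therefore stays in that set without an observed outcome and without a rule in the protocol.

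**4. Size, under an assumed share.** The protocol does not give the share *m* of patients who would have no week 12 value. Let *p* be the full-recovery proportion among those observed.

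- Lower bound (all missing counted as not recovered): (1 − m) × p
- Upper bound (all missing counted as recovered): (1 − m) × p + m
- Width: m, whatever p is

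| Assumed m | Without outcome (500 × m) | Observed | Width of bounds |
|---|---|---|---|
| 5% | 25 | 475 | 5 points |
| 10% | 50 | 450 | 10 points |
| 20% | 100 | 400 | 20 points |
| 30% | 150 | 350 | 30 points |

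The base of 500 is planned enrolment. The Main Analysis Set will be smaller, because the special groups and cases not confirmed by adjudication are left out. The counts would shrink in proportion, but for a given share the width in points is the same.

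**The case against.** The best defence is that week 12 is more than an aspiration. Section 3.1 sets follow-up at 12 weeks, section 1.6.1 classifies the outcome then, and the endpoint section calls week 12 the last visit. The volumes in section 3.6.3 are for biomarker measurement and come on top of routine tests. One can therefore read the three-sample rule as a minimum for the biobank only, with a week 12 visit and routine chemistry taken for granted.

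Part of this stands. Many patients may well have a week 12 ALT and bilirubin, and the protocol does not show that outcomes will be absent in any given number. But section 3.6.3 speaks of evaluation and sampling together, and the chemistry panel is attached to those same time-points. Nothing makes the week 12 values mandatory.

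A reader might go further and infer that week 4 values will stand in for week 12, so that slow recoverers are coded as not recovered and the AUROCs are distorted. The documents do not support this. The endpoint is fixed at week 12. The last-value rule is given only for deaths and withdrawals, and only in the Full Analysis Set. The protocol gives no recovery rates at week 4 or week 12 from which to count misclassified patients.

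Nor does it say that well outpatients stop early. The seven-sample outpatient budget gives no support to that idea, and patients who stopped because they were well would mostly be classified correctly at week 4.

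**Conclusion.** The concern holds as a conflict within the protocol: the sampling minimum and the week 12 endpoint do not fit together. A compliant patient can have a last measurement up to 56 days early and no observed primary outcome. That much follows from the text alone and can be stated with confidence.

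The size cannot be derived from the protocol. The range of 25 to 150 patients, with bounds 5 to 30 points wide, rests on an assumed share of 5% to 30% of 500. If earlier values were used in place of week 12, recovery after 4 weeks and after 12 weeks would be mixed in one endpoint. The direction and size of the resulting bias, for the recovery proportion or for any AUROC, cannot be worked out from what is given.

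**What to change.** Reconcile section 3.6.3 with section 1.6.1, section 2.1 and the primary endpoint section:

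- Make ALT and total bilirubin mandatory in a stated window around week 12, for example plus or minus 1 to 2 weeks. Routine chemistry is enough, and the third biomarker sample may keep its window of week 4 to week 12.
- Count the primary endpoint as observed only if both values fall inside that window.
- In the primary analysis, treat the outcome as missing when the last values are earlier. Use those earlier values only in a sensitivity analysis labelled as such.
- If the window runs past week 12, adjust the 12-week follow-up statement in section 3.1 to match.

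The cost is some extra follow-up effort to secure a visit that is already planned. No new assay is needed.

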### Data collection

Medical and personal data will be collected at each time-point. All these data will be recorded within the framework of the SAFE-T consortium and entered into a personal file in the test centre and saved electronically. All medical and personal data collected will be kept under strict confidentiality at the responsibility of the SAFE-T consortium. The patient’s name will never be attached to those data (completely anonymous).

1. The following data will be collected at baseline:

- Inclusion/exclusion criteria
- Diagnosis of concomitant diseases
- Screen for HAV (anti-HAV), HBV (HBs-Ag, anti-HBc or PCR), HCV (anti-HCV or PCR), HIV (anti-HIV), and HEV (anti-HEV or PCR).
- Demography, smoking history
- Liver ultrasound and Fibroscan if available.
- At least self declaration of alcohol consumption, and if justified, alcohol test (Carbohydrate Deficient Transferrin, alcohol serum concentration), drug screen and pregnancy test
- Complete blood count
- Coagulation profile (PTT, INR, TPT)
- Clinical Chemistry (total protein, albumin, BUN/urea, creatinine, ferritin, transferrin, uric acid, cholesterol, triglycerides, glucose, HbA1C, calcium, magnesium, phosphorus, sodium, potassium, chloride, bicarbonate, amylase and lipase, creatine kinase (CK), CK-MB)
- Urine Analysis (Quantitative spot urine for protein, microalbumin, and creatinine Urinalysis consisting of color &clarity, specific gravity, pH, protein, glucose, ketones, bilirubin, urobilinogen, blood, nitrite, leukocyte esterase, Urine microscopic WBC, WBC)
- Thyroid Function (TSH)

1. The following data will be collected at each time-point (including baseline):

- Current medical conditions (symptomatology, date of onset of symptoms, interval between start of medication use and liver dysfunction)
- Medication in use during the last six months before admission (date of start and dosage of medications. Use of recreational drugs and herbals)
- Physical examination including body weight, height , blood pressure and heart rate.
- Clinical Chemistry (ALT, AST, GGT, LDH, total, direct/indirect bilirubin, alkaline phosphatase, creatinine, and uric acid).
- Exploratory biomarkers, including biomarkers for FibroTest/ActiTest

1. In addition, ALT and total bilirubin may be as Pre-treatment measurement and First-on-drug measurement (prior to D0).

### Management of the blood samples

After sample’s collection, all of them will be centrifuged, the serum or plasma will be extracted and they will be stored frozen (-80°) at the study site. All biological samples

will be coded. The patient’s name will never be attached to those samples (completely anonymous). The frozen samples will be regularly sent for a centralized Biobank at Barcelona (SAFE-T Biobank) under responsibility of the SAFE-T consortium. At the SAFE-T Biobank the samples will be aliquoted in 300 microliters tubes and the biomarkers will be measured.

